### Adverse events

An adverse event (AE) is any unfavourable and unintended sign, symptom, syndrome or illness that develops or worsens during the period of observation in the study. The following will be considered adverse events:

• Fetal death

• Maternal death

An adverse event will not include:

• Itching

• Admission to hospital for delivery or fetal monitoring or operative delivery

• Congenital anomaly in the offspring of a participant in the current pregnancy

• Admission to special care baby unit (SCBU)

• A disability or incapacity

A Serious Adverse Event (SAE) is any adverse event occurring following study mandated procedures, having received ursodeoxycholic acid or placebo or waited for spontaneous term delivery that results in any of the following outcomes:

• Death

• A life-threatening adverse event

• Inpatient hospitalisation or prolongation of existing hospitalisation: Admission for delivery or fetal monitoring, induction of labour or operative deliveries in which no fetal or maternal complication occurs will not be regarded as SAE.

• A disability/incapacity

• A congenital anomaly in the offspring of a participant in the present pregnancy

Important medical events that may not result in death, be life-threatening, or require hospitalisation may be considered a SAE when, based upon appropriate medical judgment, they may jeopardise the study participant and may require medical or surgical intervention to prevent one of the outcomes listed in this definition. All adverse events will be assessed for seriousness, expectedness and causality.

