#### Safety endpoints

It is not possible to define a predetermined safety endpoint for this trial. Both treatments are in common use. All adverse events will be reported to the Data Monitoring and Ethics Committee (DMEC).

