#### Causality

*Unrelated or improbable*: a clinical event including laboratory test abnormality with temporal relationship to trial treatment administration which makes a causal relationship incompatible or for which other drugs, chemicals or disease provide a plausible explanation. This will be counted as 'unrelated' for notification purposes.

*Possible*: a clinical event, including laboratory test abnormality, with temporal relationship to trial treatment administration which makes a causal relationship a reasonable possibility, but which could also be explained by other drugs, chemicals or concurrent disease. This will be counted as 'related' for notification purposes.

*Probable*: a clinical event, including laboratory test abnormality, with temporal relationship to trial treatment administration which makes a causal relationship a reasonable possibility, and is unlikely to be due to other drugs, chemical or concurrent disease. This will be counted as 'related' for notification purposes.

*Definite*: a clinical event, including laboratory test abnormality, with temporal relationship to trial treatment administration which makes a causal relationship a reasonable possibility, and which can definitely not be attributed to other causes. This will be counted as 'related' for notification purposes.

An adverse event whose causal relationship to the study IMP is assessed by the chief investigator as 'possible', 'probable', or 'definite' is an Adverse Drug Reaction (ADR). Medical and scientific judgment shall be used in deciding whether prompt reporting is appropriate in that situation.

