#### Trial management

The management of the PITCH trial includes an element of advice that is completely independent from the principal investigators and their host institutions. We shall appoint a Trial Steering Committee (TSC) including an independent chair, an independent expert member and a lay member. The TSC will provide overall supervision of the trial, in particular, trial progress, adherence to the protocol, patient safety and the consideration of new information.

A Data Monitoring and Ethics Committee (DMEC) will be established. Members of DMEC will meet regularly to view data and the results of any interim analyses. During the pilot phase we propose that there be no formal stopping rules. However, the DMEC will review unblinded data at least annually together with all reported adverse drug reactions as they accrue. We will recruit to the pilot study for eighteen months. It will cease earlier if the DMEC recommends stopping. DMEC members will be independent of both the trial and TSC.

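### Congenital anomaly and disability are ruled out as adverse events but listed as outcomes that make an adverse event serious, and the SAE trigger does not name the early-delivery arm

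*Protocol article*

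**What the plan says.** All of the definitions stand in the Adverse events section of the protocol article.

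- The general definition of an adverse event is broad: "any unfavourable and unintended sign, symptom, syndrome or illness that develops or worsens during the period of observation in the study". Fetal death and maternal death are then named as adverse events.
- A list headed "An adverse event will not include" has five entries: itching; admission for delivery, monitoring or operative delivery; "Congenital anomaly in the offspring of a participant in the current pregnancy"; admission to the special care baby unit; and disability or incapacity.
- An SAE is an adverse event that follows procedures mandated by the study, "having received ursodeoxycholic acid or placebo or waited for spontaneous term delivery", and has one of five listed outcomes. These are death, threat to life, inpatient or prolonged hospitalisation, disability or incapacity, and "A congenital anomaly in the offspring of a participant in the present pregnancy". Important medical events may be added on judgement.

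Reporting follows from these terms. Safety endpoints sends all adverse events to the DMEC and gives no timing. Reporting of adverse events sends SAEs to the chief investigator at once and to the MHRA and REC in annual reports. The SUSAR section adds expedited reporting for SAEs that are unexpected and suspected to be related to the drug. Trial management has the DMEC "review unblinded data at least annually together with all reported adverse drug reactions as they accrue".

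**The concern.** The same event is ruled out by one list and required by the next. A site that applies the first list stops before it reaches the second, and a site that starts from the SAE list reports. Both can say that they followed the protocol.

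The harms concerned are ones the protocol itself worries about. Its Background says that the drug's safety for the fetus has not been adequately tested. It also names brain damage from prematurity caused by early delivery as a possible harm.

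The delivery comparison raises a second worry. It is open-label, and only one of its two arms is named in the SAE trigger. If sites read the trigger differently, reporting could differ by arm as well as by centre.

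**Working it through.** No figure is involved, so the check sets the texts side by side.

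**Step 1: how the definitions nest.** An SAE is defined as an adverse event with further properties. Anything that is not an adverse event therefore cannot be an SAE, nor a SUSAR, which is a kind of SAE.

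**Step 2: the exclusion list against the SAE outcomes.**

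| Item | Adverse event? | SAE outcome? | Result |
|---|---|---|---|
| Congenital anomaly in the offspring | Excluded | Yes | Contradiction, with almost no way round it: the anomaly is itself the event |
| Disability or incapacity | Excluded | Yes | Contradiction if taken as the event; not if it results from another adverse event, such as a neonatal illness |
| Operative delivery | Excluded, with no condition | Carved out only if no fetal or maternal complication occurs | Unclear: the first entry can mean only admission for that purpose, but says nothing about complications |
| Special care baby unit admission | Excluded | Not named, though hospitalisation is an outcome | Awkward, but not a direct contradiction |
| Fetal death | Named as an adverse event | Yes, as death | Consistent |

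Two of the five SAE outcomes are thus also on the exclusion list.

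**Step 3: the SAE trigger against the allocations.** The two comparisons have four arms: ursodeoxycholic acid, placebo, early planned delivery and await spontaneous labour. The trigger names three of the four. By type of participant:

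- Drug comparison only, or both comparisons: covered by having received drug or placebo, whatever the delivery arm.
- Delivery comparison only, waiting arm: covered by name.
- Delivery comparison only, early arm: covered only if planned early delivery counts as a procedure mandated by the study.

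The Randomised procedure section lets women between 34+1 and 37+6 weeks choose one comparison or both, so the last group can exist.

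**Step 4: the route to the DMEC.** Safety endpoints covers all adverse events but sets no timing. Trial management mentions flow as events accrue only for adverse drug reactions. Causality ties those to the drug: "An adverse event whose causal relationship to the study IMP is assessed by the chief investigator" as possible, probable or definite. A woman in the delivery comparison alone takes no trial drug and cannot have such a reaction. Her events reach the DMEC by the general commitment, at a time that the article does not state. Annual review is a minimum, and recruitment lasts eighteen months, so a single unblinded review during recruitment would satisfy it.

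**The case against.** The strongest reply is that these are drafting faults and that the system around them is sound. Much of that stands.

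- Disability keeps a route. The general definition includes any illness, so a neonatal illness that ends in disability is an adverse event and then an SAE.
- Early planned delivery is a randomised, planned intervention, and reading it as a mandated procedure is reasonable. Waiting is not a procedure, which may be why it is named separately. A reader might infer that the early arm is excluded from SAE reporting; the text does not say so.
- The two DMEC statements can be read as additive. A reader might infer that between annual reviews the DMEC sees only adverse drug reactions, but Trial management does not say only, and it also has members meeting regularly.
- A reader might infer that key fetal harms would go unreported altogether. Fetal death is a named adverse event and an SAE.
- A reader might infer that harm could not be compared between arms. Discharge and six-week outcome forms are completed for participants without regard to arm, and the DMEC sees unblinded data. The content of those forms is not shown, so nothing can be said about what they lack.
- A reader might infer that only the DMEC can bring about an early stop for safety. The SUSAR section lets the chief investigator halt the trial, and the sponsor may discontinue it for safety, taking advice from the steering committee as well as the DMEC.

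The reply does not remove the contradiction. The trials unit's adverse-event procedure, to which the article refers, may guide sites, but the protocol's own definitions would still say two things. Nor is this a matter left out by condensing: both lists are printed.

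**Conclusion.** The point holds as a contradiction within the safety definitions, with two ambiguities beside it. Two of the five SAE outcomes are also listed as not being adverse events: the conflict is near-complete for congenital anomaly and partial for disability. One of the four randomised arms is not named in the SAE trigger, which matters chiefly for women in the delivery comparison alone. The timing with which their SAEs reach the DMEC is also unstated.

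The supported consequence is inconsistent classification and reporting between sites, and possibly between delivery arms. It is not a loss of all reporting. How many events would be affected cannot be estimated from the article. The recruitment endpoints are untouched. The conclusion assumes that sites apply the printed definitions, and that the full protocol or the trials unit's procedure does not already resolve them. Contradictory safety definitions in a drug trial in pregnancy still need correcting, and the correction is cheap.

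**What to change.** 1. Remove congenital anomaly and disability or incapacity from the list of exclusions, or otherwise reconcile that list with the SAE outcomes so that each event has one classification.
2. Align the operative-delivery wording in the two lists so that a fetal or maternal complication is clearly reportable.
3. Word the SAE trigger to cover every randomised arm of both comparisons, for example any event after randomisation to either comparison, in any arm.
4. Align Safety endpoints with Trial management so that it is clear that SAEs from both comparisons, and not only adverse drug reactions, reach the DMEC, and when.

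The cost is protocol and safety-form wording and a few more SAE forms in a pilot of about 90 women. No treatment, visit or endpoint changes.

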#### Seriousness

A distinction is drawn between serious and severe adverse events. Severity is a measure of intensity whereas seriousness is defined using the criteria above. Hence, a severe adverse event need not necessarily be serious.

#### Causality

*Unrelated or improbable*: a clinical event including laboratory test abnormality with temporal relationship to trial treatment administration which makes a causal relationship incompatible or for which other drugs, chemicals or disease provide a plausible explanation. This will be counted as 'unrelated' for notification purposes.

*Possible*: a clinical event, including laboratory test abnormality, with temporal relationship to trial treatment administration which makes a causal relationship a reasonable possibility, but which could also be explained by other drugs, chemicals or concurrent disease. This will be counted as 'related' for notification purposes.

*Probable*: a clinical event, including laboratory test abnormality, with temporal relationship to trial treatment administration which makes a causal relationship a reasonable possibility, and is unlikely to be due to other drugs, chemical or concurrent disease. This will be counted as 'related' for notification purposes.

*Definite*: a clinical event, including laboratory test abnormality, with temporal relationship to trial treatment administration which makes a causal relationship a reasonable possibility, and which can definitely not be attributed to other causes. This will be counted as 'related' for notification purposes.

An adverse event whose causal relationship to the study IMP is assessed by the chief investigator as 'possible', 'probable', or 'definite' is an Adverse Drug Reaction (ADR). Medical and scientific judgment shall be used in deciding whether prompt reporting is appropriate in that situation.

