## Background

Obstetric cholestasis (OC) is a liver condition unique to pregnancy. It is also referred to as Intrahepatic Cholestasis of Pregnancy (ICP). Pruritus is the characteristic symptom [1,2] accompanied by otherwise unexplained deranged liver enzymes [3-7] and elevated serum bile acid levels [3,7-9]. The itching subsides almost immediately after delivery [1,2,10] and the serum bile acid levels and the liver enzymes normalise within 2–3 weeks of delivery [1,10-14]. Occasionally, a patient might present with atypical symptoms such as jaundice, steatorrhoea, nausea, vomiting, anorexia, hepatomegaly and megalosplenia [15]. It is typically seen in the late second and third trimester [11,16,17] although some studies have reported presentation as early as six to ten weeks gestation [13,18].

Obstetric cholestasis affects between 0.7% and 1% [19]of pregnancies in the UK. It runs a relatively benign course in the mother. The main concern is its association with increased rates of perinatal mortality [1,5,11-14,17,20-24] and spontaneous preterm labour [11-13,17,20,21,23-25]

Most UK obstetricians treat obstetric cholestasis with ursodeoxycholic acid [26] in the belief that it reduces itching although this has not been shown in a suitably sized randomised controlled trial (RCT). Nor has fetal benefit or safety been adequately tested [27,28]. The latest Cochrane review, updated in 2001 [29] included three trials [30-32] involving 56 women comparing ursodeoxycholic acid with placebo. No statistically significant benefit on pruritus, or fetal outcomes was demonstrated. Since then a further trial [28] randomised 130 women diagnosed with obstetric cholestasis to placebo, ursodeoxycholic acid or dexamethasone. The only statistically significant effects in the groups as randomised were beneficial biochemical changes in the ursodeoxycholic acid group. In the subgroup with the highest bile acids at entry, ursodeoxycholic acid was associated with reduced pruritus. Although the only fetal death occurred in the placebo group, there was a non-significant trend towards more meconium in the ursodeoxycholic acid group. The latest guidelines from the RCOG (RCOG Guideline No. 43, January 2006) conclude as follows

"There are insufficient data to support the widespread use of ursodeoxycholic acid outside of clinical trials. Women should be aware of the lack of robust data concerning improvement in pruritus, protection against stillbirth and safety to the fetus or neonate."

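### The 'unrelated' and 'possible' causality categories overlap, so a fetal death on study drug that cholestasis could explain may be rated either way, with opposite notification consequences

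*Protocol article*

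**What the plan says.** The Causality section of the protocol article sets out four categories.

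- *Unrelated or improbable* covers an event with a timing "which makes a causal relationship incompatible or for which other drugs, chemicals or disease provide a plausible explanation". The consequence is stated: "This will be counted as 'unrelated' for notification purposes".
- *Possible* covers an event whose timing "makes a causal relationship a reasonable possibility, but which could also be explained by other drugs, chemicals or concurrent disease". This is counted as related.
- *Probable* and *definite* also require a reasonable possibility of causation, with other causes unlikely or excluded. Both are counted as related.

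The same section then says that an event whose link to the study drug is "assessed by the chief investigator as 'possible', 'probable', or 'definite' is an Adverse Drug Reaction (ADR"). The section on SUSARs reserves expedited reporting for serious events related, or suspected to be related, to the study drug.

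Two places describe what the DMEC receives. Safety endpoints says "All adverse events will be reported to the Data Monitoring and Ethics Committee (DMEC"), with no timetable. Trial management says "the DMEC will review unblinded data at least annually together with all reported adverse drug reactions as they accrue".

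On the disease, the Background says "The main concern is its association with increased rates of perinatal mortality". The Abstract ties the condition to premature delivery and fetal distress, and calls it a believed cause of stillbirth.

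**The concern.** A causality scale works only if an event with given features falls in one category. Here the dividing line between related and unrelated runs between two categories that share ground, and the shared ground is a disease explanation.

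That matters in this trial because the disease under study is a ready explanation for the fetal events of most interest. The Abstract also says it is not known whether ursodeoxycholic acid is safe in pregnancy. The scale is therefore ambiguous where the safety question lies. Two assessors could rate the same fetal death differently, both following the text. One rating would lead to drug-reaction status and possibly expedited reporting, and the other would not.

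**Working it through.** No arithmetic applies, so the check is logical. Take two features of an event, whether its timing makes causation a reasonable possibility and whether disease or another agent could plausibly explain it, and apply the definitions as printed.

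| Causation a reasonable possibility on timing? | Plausible other explanation? | Categories met | Counted as |
|---|---|---|---|
| No, timing incompatible | No | Unrelated (first limb) | Unrelated |
| No, timing incompatible | Yes | Unrelated (both limbs) | Unrelated |
| Yes | Yes | Unrelated (second limb) **and** possible | **Both** |
| Yes | No, unlikely or excluded | Probable or definite | Related |

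Only the third row fails. The second limb of 'unrelated' asks for a plausible explanation by disease and says nothing about whether the drug remains a reasonable possibility. The condition in 'possible', "but which could also be explained by other drugs, chemicals or concurrent disease", describes the same situation. Nothing in the section says which prevails.

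Now place a fetal death on study drug, with compatible timing, in that row. The Adverse events section names fetal death as an adverse event and death as a criterion of seriousness; I assume a fetal death meets that criterion. The two permitted ratings then lead to different routes.

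| Step | Rated possible | Rated unrelated |
|---|---|---|
| Notice to the Chief Investigator (Reporting of adverse events) | Immediate | Immediate |
| Adverse drug reaction (Causality) | Yes | No |
| SUSAR (section on SUSARs) | Yes, if also unexpected: MHRA and REC within seven days | No, once judged unrelated |
| MHRA and REC if not a SUSAR (Reporting of adverse events) | Annual reports | Annual reports |
| DMEC running review (Trial management) | Yes | Not named |
| DMEC, all adverse events (Safety endpoints) | Yes, timing not given | Yes, timing not given |

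The rating thus changes three things: drug-reaction status, access to the expedited route, and the DMEC's running review. It does not change whether the Chief Investigator is told, or whether the DMEC eventually receives the event.

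The running review is also tied to drug reactions, which the Causality section defines by relation to the study drug. An event attributable only to the delivery allocation therefore falls outside it, although the definition of a serious adverse event expressly includes women who waited for spontaneous labour.

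**The case against.** The best case for the plan is that its other provisions contain the ambiguity.

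- All three related categories turn on a reasonable possibility of causation, so a sensible assessor would take that as the dividing line. This is probably what was intended, but the printed definition of 'unrelated' does not say so.
- The section on SUSARs has serious events suspected of meeting its criteria handled as SUSARs until judged otherwise. This is a real safeguard. The later judgement, however, is made on the same overlapping scale.
- Every serious adverse event goes at once to the Chief Investigator, who judges causality together with the treating practitioners, and the trials unit's standard operating procedure applies. That procedure is not shown and may settle operational timing. It does not alter the definitions printed here.
- Safety endpoints sends all adverse events to the DMEC, and Trial management says the committee meets regularly. This stands and limits the point.

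Some stronger readings are tempting and should not be drawn.

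- A reader might infer that any event with a disease explanation is automatically filed as unrelated. It is not, because the same event also meets 'possible'. The defect is ambiguity.
- A reader might infer that nearly all fetal events would be affected. The documents give no such frequency.
- A reader might apply the 6% composite rate in Statistics to the pilot's roughly ninety women to count affected events. That rate is a provisional main-trial assumption for fetal death or severe morbidity combined, and the same section says the clinical spectrum is not yet known.
- A reader might infer that an event rated unrelated is kept from the DMEC until an annual review. Trial management does not say that drug reactions are all the committee sees between reviews, annual review is a minimum, and Safety endpoints covers all adverse events. Only the timing is left open.

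**Conclusion.** The point holds as an overlap between two categories with opposite notification consequences and no tie-break. It affects any event with compatible timing that disease could plausibly explain, and by the protocol's own account of obstetric cholestasis this can include a fetal death on study drug. Such a death may be rated unrelated within the text. It would then not be an adverse drug reaction, would miss expedited SUSAR reporting, and would miss the DMEC's review of drug reactions as they arise. The DMEC is still owed the event under Safety endpoints, without a stated time.

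The number of events affected cannot be derived from the documents. The conclusion rests on the printed definitions, on the assumption that a fetal death counts as serious, and, for the SUSAR route, on the event also being unexpected. It should be corrected, since it is a stated safety rule that does not work as written and the correction is small.

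**What to change.** In Causality:

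- Define 'unrelated or improbable' as an event for which a causal relationship is not a reasonable possibility. Incompatible timing alone is enough; a plausible alternative explanation alone is not. Requiring both would leave an event with incompatible timing and no known cause in no category.
- State that any event for which a causal link is a reasonable possibility is at least 'possible', even if cholestasis could also explain it.

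In Trial management, reconcile the DMEC sentence with Safety endpoints. After adverse drug reactions, add: *and all serious adverse events, including fetal deaths, in either comparison, whatever the causality assessment, as they accrue*. This should add to drug reactions, not replace them; otherwise non-serious drug reactions would drop out of the running review.

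The cost is a few sentences. The downside is that a few more events among about 90 women would be classed as related and forwarded.
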